#### Family members/Informal carers questionnaires

Patients’, family members/ informal carer complete socio-demographic variables and an outcome measurement tool for carers (CBS-EOLC). Repeated assessment will be carried out using the same tools (time points).

### Additional data

Each participating site will collect information about volunteer visits and record per patient participant details such as: referral date, consent date, allocation arm, dates of assessments date allocated to a volunteer, first date of volunteer visit, dates/numbers of volunteer visits and brief indication of support given and dates/numbers of volunteer support through calls/texts or skype.

A schedule of enrolment, interventions and assessment of outcomes is provided in Table 1.

**Table 1 Tab1:**
[figure not shown]
ELSA: Schedule of enrolment, interventions, and assessments

(X) indicates that week 12 data are only collected for those in the wait arm of the trial (8 weeks after commencement of intervention)

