**Methods/design:**

The research questions will be addressed through a wait-list randomised controlled trial (WLRCT) and qualitative case study evaluation across 12 sites in England. Participants will be randomly allocated to either receive the social action volunteer befriending service straight away or receive the intervention after a four week wait (wait-list arm). The impact of the intervention on end-of-life experience (quality of life as primary outcome, loneliness, social support) will be measured. Repeated assessments will be carried out at baseline and weeks 4 and 8 for the intervention arm and weeks 4, 8 and 12 for the wait-list arm. For selected sites case study evaluation will include interviews, observation and documentary analysis to understand the mechanisms underpinning any found impact.

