### The intervention

The intervention is based on a model of social action, and comprises a number of components. Core to the intervention is that it is provided by a trained volunteer rather than a paid member of staff, and provides non-clinical, non-hands on support. Individual support needs are assessed by the non-clinical volunteer co-ordinator, and support then provided from a suite of possible options including ‘befriending’ e.g. sitting with someone to provide companionship, ‘practical support’ e.g. assisting with household tasks such as dog walking, gardening, picking up prescriptions or other errands, and ‘signposting’ e.g. providing information on other available services. Support will be typically provided from 1–3 times per week, face to face or by telephone, as negotiated between volunteer providers and participants. Participants will be in the trial for 8 or 12 weeks (immediate vs wait-list arm), but their receipt of the social action volunteer service can continue outside the trial beyond this point if needed. Participants are free to withdraw at any time. Participants will continue to receive all usual care during this period. In this study the intervention will be provided across a number of sites in England who are independently funded to provide this service by the UK Cabinet Office.

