### Participant timeline

#### Patient questionnaires

Baseline data (including socio-demographic data such as age, gender, disease diagnosis, education, marital status, living status, spirituality and ethnicity) will be collected from both patients and carers prior to randomisation. The patients randomised to immediately receive the service will do so (following any service administrative procedures) and continue to receive it for as long as required as assessed by the service providers in conjunction with service recipients. At week 4 all participants (intervention arm and wait-list arm) will complete the outcome measures. At this point, the patients on the wait-list arm will also commence receiving the service. Measures will be repeated at week 8. those on the wait-list arm will complete an additional questionnaire at week 12. Participants who withdraw from the service will not be required to complete questionnaires as this may be due to deterioration in physical condition, and the risk of sending questionnaires inappropriately if the services are unable to provide updates on their health status.

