### Comparison between arms

Data will be analysed on an intention to treat basis. A linear mixed effect model (LME) will be fitted to each outcome variable at 4, 8 and 12 weeks. The random effects are intercept and slope; which posit that each participant has a “personalized” linear response to treatment. The fixed effects include site, treatment group, and time since entry, and time interactions, which measure systematic differences in the rate of change. The assumption of a common initial mean for all participants is justified by the randomization of participants into treatment groups. A major advantage of the LME model is that is does not require a balanced design; in particular, participant effects can be estimated using incomplete data. However, missing-completely-at-random (MCAR) assumption will be tested, and in case that this assumption is not tenable, multiple imputation procedures will be employed.

Analyses will be conducted to evaluate potential variables associated with dropout in wait-list controls, to prevent that this attrition inflates the apparent treatment effect at 4 weeks by comparing the intervention group with only those in the wait-list group with some particular features. If observed, these confounders will be included in the LME model to reduce the bias of differential attrition on the estimated treatment effect.

Statistical significance will be assessed at the 5 % (two-sided) level. All statistical analyses will be conducted using SPSS v.20.

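### Week 12 is measured only in the wait-list arm, yet it enters a between-arm model with linear time, where it can bias the group-by-time estimate

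*Protocol article*

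**What the plan says.** The schedule is stated consistently. The abstract plans assessments at "baseline and weeks 4 and 8 for the intervention arm and weeks 4, 8 and 12 for the wait-list arm". The section The intervention gives the matching time in trial: 8 weeks for the immediate arm and 12 for the wait-list arm. Patient questionnaires confirms that "those on the wait-list arm will complete an additional questionnaire at week 12". The Table 1 footnote says that "week 12 data are only collected for those in the wait arm of the trial", and places that visit 8 weeks after the wait-list arm starts the service.

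The wait-list arm crosses over at week 4. After describing the week-4 assessment, Patient questionnaires continues: "At this point, the patients on the wait-list arm will also commence receiving the service".

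The analysis is under Comparison between arms: "A linear mixed effect model (LME) will be fitted to each outcome variable at 4, 8 and 12 weeks". Its random effects are an intercept and a slope, giving each participant a linear response. On the fixed part it says: "The fixed effects include site, treatment group, and time since entry, and time interactions, which measure systematic differences in the rate of change". It assumes a common baseline mean and counts tolerance of an unbalanced design as an advantage. The only treatment effect it ties to a time point is the one at 4 weeks.

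**The concern.** A visit that only one arm attends cannot give a between-arm comparison at that visit. Its data can reach the treatment estimate only through the shape imposed on time. With a straight line per arm, the wait-list line is fitted over 0 to 12 weeks and the immediate-arm line over 0 to 8. If the true course is curved and identical in both arms, the two fitted slopes differ although the service does nothing.

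Curvature is plausible here. Participants are thought to be in their last year of life, and the design section itself expects substantial loss to illness and death. If decline accelerates, the false difference favours the service. If decline slows, it goes the other way. At stake is the test of the group-by-time term for the primary quality-of-life outcome and for every secondary outcome given the same model.

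**Working it through.** **Inputs from the protocol** (Trial power calculation and sample size): 350 per arm, 5% attrition, two-sided alpha .05, f = .10, correlation .6 at 4 weeks and .5 at 12 weeks. **Assumed:** correlation .55 at 8 weeks (not given), SD 1, and the mean trajectories below. Analysed per arm: n = 350 × 0.95 = 332.5.

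**1. The plan's own figure.** For two groups d = 2f = 0.20. The change-score SD with r = .6 is √(2(1 − .6)) = 0.894. SE = 0.894 × √(2/332.5) = 0.0694. Power = Φ(0.20/0.0694 − 1.96) = 0.82. The stated power above .80 reproduces on this reading and does not use week 12. With r = .5 the same formula gives 0.73.

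**2. Is there a week-12 contrast?** The schedule gives 1 pooled baseline mean, 2 means at week 4, 2 at week 8 and 1 at week 12, so 6 cells. A model with a contrast at weeks 4, 8 and 12 needs 7 parameters: the baseline, three wait-list means and three contrasts. The design has rank 6 of 7, so the week-12 contrast is not estimable.

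**3. Visit-specific means, common baseline** (generalised least squares). The SE of a contrast at lag t is √(2(1 − r_t²)/n).

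- Week 4: √(2 × 0.64/332.5) = 0.0620 SD.
- Week 8: √(2 × 0.6975/332.5) = 0.0648 SD.
- Both are identical with and without the wait-list week-12 data.
- With an assumed 10 to 30% intermittent non-response at each of weeks 4 and 8, adding week 12 lowers these SEs by 1% or less.
- For a constant service effect, the SE is 0.0568 SD with weeks 0/4/8, 0.0568 when week 12 is added in the wait-list arm only, and 0.0554 with week 12 in both arms.

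**4. Linear time by group, common baseline, no treatment effect.** The assumed means in both arms are 0, -.05, -.15, -.30 SD at weeks 0, 4, 8, 12.

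| Week 12 collected in | Slope difference per week | SE | Rejection at 5% |
|---|---|---|---|
| Neither arm | 0 | 0.0080 | 5% |
| Wait-list only (as planned) | 0.0055 | 0.0069 | 12.7% |
| Both arms | 0 | 0.0054 | 5% |

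For the planned row, λ = 0.00552/0.00686 = 0.804, and Φ(0.804 − 1.96) + Φ(−0.804 − 1.96) = 0.127. Over 8 weeks the false difference is 8 × 0.0055 = 0.044 SD in favour of the immediate arm.

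The bias is proportional to the assumed means. Halving them gives λ = 0.402 and rejection of Φ(−1.558) + Φ(−2.362) ≈ 6.9%. A strictly linear shared decline gives no bias.

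**5. The estimate also moves when there is an effect.** Week 12 changes the linear slope difference as follows.

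- Benefit growing 0.05 SD per week on service: 0.0268 to 0.0179 per week (about −33%), power 0.92 to 0.74.
- Benefit a flat 0.2 SD step: 0.00362 to 0.00777 per week (about +115%), power 0.07 to 0.21.

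**The case against.** The strongest reply is that the schedule is deliberate. It is stated the same way throughout, and it follows each arm to 8 weeks of scheduled service. The protocol is right to limit questionnaires for dying patients, and a mixed model does accept unequal follow-up. All of this stands: the schedule is neither an error nor a contradiction. But tolerance of imbalance means that the model can be fitted. It does not protect a linear time term when only one arm supplies the last visit.

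A statistical analysis plan could also code time differently. That is possible, but the article itself puts 12 weeks in the between-arm model and describes linear responses and rates of change. No analysis plan can recover immediate-arm week-12 data that were never collected.

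Several stronger readings are tempting and not supported:

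- **Week 12 adds nothing to any randomised estimate, whatever the model.** This is true of visit-specific means. In the linear model described, week 12 moves the estimate.
- **The plan compares wait-list week 12 with immediate-arm week 8 as evidence of effect.** The footnote gives only timing. No section states that comparison, so it is an inference.
- **Week 12 serves no stated aim.** One secondary aim is to explore factors that influence impact, and within-arm course on the service can inform that descriptively.
- **Catch-up after waiting cannot be studied.** Week 8 is concurrent in both arms (8 versus 4 weeks of service by schedule) and already bears on it. The risk named under Risks concerns the waiting period, which week 4 addresses.

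It is also fair to say that collecting week 12 in both arms buys little precision: 0.0568 to 0.0554 SD is about 2.5%. Nor would it make a straight line the right shape for an effect interrupted by crossover at week 4.

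**Conclusion.** The point holds as a mismatch between the schedule and the between-arm model. Week 12 has no concurrent comparator and supports no randomised contrast. With visit-specific means it is essentially idle. In the linear model as written it can bias the group-by-time estimate whenever the shared course over time is not linear.

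The mechanism follows from the design, but its size does not. The 12.7% rejection rests on one assumed accelerating decline, an assumed 8-week correlation of .55, 332.5 per arm at every visit, and the power section's correlations standing in for the random-effects covariance. A straighter course gives less, down to none. The randomised week-4 contrast is unharmed if week 12 is kept out of the slope, and the power statement does not depend on week 12. The change is worth making, but the trial's main comparison is not lost without it.

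**What to change.** Choose one of two changes.

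1. **Collect week 12 in both arms.** Report it as a randomised comparison of immediate with delayed start (12 versus 8 weeks of service by schedule). By the formula in step 3, its SE would be √(2 × 0.75/332.5) = 0.067 SD with full returns. The cost is one more posted form for surviving immediate-arm patients and their carers, with thinner returns by then and only a small gain in precision for the overall effect.
2. **Leave the schedule alone and change Comparison between arms.** Keep week 12 out of the between-arm model, treat time as categorical, and take week 4 as service versus usual care and week 8 as immediate versus delayed start. Label wait-list week-12 results as non-randomised and descriptive, including any set beside immediate-arm week 8 on service time. Those respondents are 4 weeks further into illness and have survived and stayed in that much longer. The cost is a text change only.

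Neither option needs more patients or staff.

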## Data analysis

### Descriptive analyses

Exploratory data techniques will be used to examine all distributions of outcome variables Continuous data will be summarised using means and standard deviations (SD) if normally distributed and medians and interquartile ranges (IOR) if non-normally distributed. Categorical data will be described using frequencies and percentages.

### Comparison between arms

Data will be analysed on an intention to treat basis. A linear mixed effect model (LME) will be fitted to each outcome variable at 4, 8 and 12 weeks. The random effects are intercept and slope; which posit that each participant has a “personalized” linear response to treatment. The fixed effects include site, treatment group, and time since entry, and time interactions, which measure systematic differences in the rate of change. The assumption of a common initial mean for all participants is justified by the randomization of participants into treatment groups. A major advantage of the LME model is that is does not require a balanced design; in particular, participant effects can be estimated using incomplete data. However, missing-completely-at-random (MCAR) assumption will be tested, and in case that this assumption is not tenable, multiple imputation procedures will be employed.

Analyses will be conducted to evaluate potential variables associated with dropout in wait-list controls, to prevent that this attrition inflates the apparent treatment effect at 4 weeks by comparing the intervention group with only those in the wait-list group with some particular features. If observed, these confounders will be included in the LME model to reduce the bias of differential attrition on the estimated treatment effect.

Statistical significance will be assessed at the 5 % (two-sided) level. All statistical analyses will be conducted using SPSS v.20.

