## Methods/design

### Aims

The **primary aim** of the study is to evaluate the effectiveness of receiving care from a social action volunteer befriending service plus standard care at improving quality of life as compared to usual care alone for adults in the last year of life.

The **secondary aims** are to:explore whether the social action volunteer befriending service reduces loneliness and affects the perception of social support for adultsexamine whether informal carers for those receiving care from a social action volunteer befriending service experience less carer burdendetermine whether receiving care from a social action volunteer befriending service can affect participant’s use of other health and social care servicesidentify and explore the factors that influence the impact of social action volunteer befriending services on end-of-life experience

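### The planned group-by-time slope uses weeks 4, 8 and 12 with no term for the wait-list arm starting the service at week 4, so it does not estimate service versus usual care alone

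*Protocol article*

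**What the plan says.** The Aims section sets the service plus standard care against usual care, "as compared to usual care alone for adults in the last year of life".

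Comparison between arms describes one model for every outcome: "A linear mixed effect model (LME) will be fitted to each outcome variable at 4, 8 and 12 weeks". On its structure it says "The random effects are intercept and slope", so that each participant has an individual linear response. It continues: "The fixed effects include site, treatment group, and time since entry, and time interactions, which measure systematic differences in the rate of change". It adds: "The assumption of a common initial mean for all participants is justified by the randomization of participants into treatment groups".

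The timeline under Patient questionnaires says of week 4: "At this point, the patients on the wait-list arm will also commence receiving the service". The footnote to Table 1 says that "week 12 data are only collected for those in the wait arm of the trial (8 weeks after commencement of intervention").

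**The concern.** The arms differ in the way the aim requires only from baseline to week 4. After that both receive the service, so the wait-list arm's later change contains whatever the service does. At week 12 there is no immediate-arm measurement to compare with, and that visit informs only the slope of the wait-list arm while it is being treated.

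If the service works, the wait-list trajectory (untreated, then treated) will in general not be one straight line. A model that gives each randomised group a single slope averages the two phases. Its group-by-time coefficient is then a mixture of treated-versus-untreated and treated-versus-treated-later.

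This is the analysis of the primary outcome. A useful service could be reported as having no effect because the comparator was also receiving it for most of the modelled period.

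**Working it through.** **Inputs.** From Trial power calculation and sample size: 350 per arm, 5% attrition, f = .10, two-sided alpha .05, r = .6 at a 4-week lag and .5 at 12 weeks. From the timeline and Table 1: immediate arm at weeks 0, 4, 8; wait-list arm at weeks 0, 4, 8, 12, with service from week 4. Assumptions: r = .55 at 8 weeks; d = 2f = 0.20 SD as the effect after 4 weeks of service; the shape of the effect over time.

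**1. The plan's own power figure.** Analysed per arm: 350 × 0.95 = 332.5.
- Week-4 change score: SD = √(2(1 − .6)) = .894; SE = .894 × √(2/332.5) = .0694; z = 0.20/.0694 = 2.88; power .82.
- Week-4 comparison adjusted for baseline: SD = √(1 − .6²) = .80; SE = .0620; z = 3.22; power .90.

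The stated power above .80 therefore reproduces for a comparison made before the wait-list arm is treated.

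**2. Hand check of the slope difference** (ordinary least squares, effect at 4 weeks of service = 1).
- Effect complete by 4 weeks and then held. Immediate arm 0, 1, 1: slope = 4/32 = 0.125 per week. Wait-list arm 0, 0, 1, 1: slope = (2 + 6)/80 = 0.100 per week. Difference × 4 weeks = 0.10.
- Effect growing linearly. Immediate arm 0, 1, 2: (4 × 2)/32 = 0.250 per week. Wait-list arm 0, 0, 1, 2: (2 × 1 + 6 × 2)/80 = 0.175 per week. Difference × 4 weeks = 0.30.

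**3. Generalised least squares with the correlations above.** The true arm means were projected onto intercept, time and arm × time. This was done once with a free arm difference at baseline (treatment group is listed as a fixed effect) and once with the stated common initial mean. The SE of the slope difference per 4 weeks is .0315 and .0275 respectively.

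| Assumed effect | Baseline | Slope difference per 4 weeks | Share of 0.20 SD | z | Power |
|---|---|---|---|---|---|
| Complete by 4 weeks, held | free | 0.021 SD | 10–11% | 0.67 | .10 |
| Complete by 4 weeks, held | common | 0.031 SD | 16% | 1.13 | .20 |
| Growing linearly | free | 0.060 SD | 30% | 1.92 | .49 |
| Growing linearly | common | 0.071 SD | 36% | 2.60 | .74 |

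Other correlation structures (exchangeable, autoregressive, random intercept and slope) without dropout gave 10–18% and 30–37%. With heavy dropout the two shapes together ranged from 15% to 43%.

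**4. A mainly delayed effect.** With 0.05 SD after 4 weeks of service and 0.30 SD after 8, the slope difference is 0.055–0.058 SD, no smaller than the week-4 effect. With 0.05 and then 0.20 SD, it is 0.035–0.038 SD, about 70–76% of the week-4 effect.

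**5. No treatment effect, decline common to both arms** (weeks 0, 4, 8, 12, in SD).
- Linear, 0, −0.05, −0.10, −0.15: no bias, rejection 5%.
- Mildly accelerating, 0, −0.02, −0.06, −0.12: slope difference 0.009–0.010 SD, rejection 6%.
- Strongly accelerating, 0, −0.05, −0.15, −0.35: slope difference 0.035–0.040 SD in favour of the immediate arm, rejection about 25%.

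**The case against.** The strongest reply is that a slope over weeks 0–12 is only one reading. The paragraph on dropout in Comparison between arms speaks of the apparent treatment effect at 4 weeks. The sample size fits a week-4 comparison. Whether time in the fixed effects is linear or categorical is not stated outright. If visit-specific contrasts were meant, the week-4 one would be clean. A condensed article may also leave the primary time point and the coding of time to a fuller document, so their absence alone is no fault.

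That last point stands, and the criticism is confined to what is written. The rest does not rescue the model. The week-4 effect is mentioned only as something that dropout might distort and is not set as the primary contrast. What the interactions are said to measure is a rate of change. The model cannot be read as baseline to week 4 either. The text names weeks 4, 8 and 12. Two visits also give three variance and covariance terms, against four parameters for correlated random intercepts and slopes plus residual error. The article's remark that mixed models tolerate unbalanced data concerns incomplete observations; it does not correct a mean structure that ignores a change of treatment.

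Two objections on size also stand. Omitting the common initial mean gives only the less favourable figures, so both versions are shown. And every loss quoted depends on an assumed effect shape.

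**Conclusion.** The point holds in this form: the model as described does not estimate the service plus usual care against usual care alone, a contrast that randomisation protects only up to week 4. Under the stated assumptions, the slope per 4 weeks keeps about 10–16% of an effect complete by 4 weeks (power .10–.20) and 30–36% of a linearly growing one (power .49–.74). The week-4 contrast keeps the full 0.20 SD with power .82–.90.

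Two stronger conclusions that a reader might draw are not supported. The first is that the plan must lose most of any true effect. It need not: a mainly delayed effect is diluted little or not at all relative to week 4, and the document gives no effect shape. The second is that the analysis has a false-positive rate of around 25%. A common accelerating decline can bias the slope difference towards the immediate arm, but that figure belongs to one assumed trajectory. A linear decline gives 5% and a mildly accelerating one 6%, and the document gives no trajectory. This part is illustrative only.

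**What to change.** Name the week-4 between-arm difference in overall quality of life as the single primary contrast and the only test at 5%. Fit time as categorical (0, 4, 8, 12) with arm-by-visit terms, keeping the common baseline mean already stated. An analysis of covariance of week 4 on baseline would also serve. Report week 8 as immediate versus 4-week-delayed start. Report week 12 as within-arm description, or use it in a secondary model in which exposure to the service changes over time.

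The cost is a reworded analysis section and a different model specification, with no new data. The model has a few more parameters, and data after week 4 no longer contribute to the primary test as a slope would have let them. The existing sample size matches this contrast.

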#### Randomisation of patients in the trial

Once written informed consent has been obtained to participate in the trial, and baseline data collected, patients will be randomly allocated (1:1 allocation ratio) to either the intervention or the wait-list arm of the trial. Site coordinators will contact a randomisation line at Lancaster University, and the next sequence in the allocation (stored in sequentially numbered sealed opaque envelopes) will be revealed. The randomisation sequence will be computer generated by an experienced statistician outside the study context, with rebalance in the arms after 10 randomisations. Blinding of site staff and patient participants will not be possible due to the nature of the intervention.

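### The model description asserts a common initial mean but lists a free treatment-group effect and no baseline score, so the primary model, and how far it uses baseline, is unresolved

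*Protocol article*

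**What the plan says.** The Comparison between arms section of the protocol article makes four statements about the model:

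- Time points: "A linear mixed effect model (LME) will be fitted to each outcome variable at 4, 8 and 12 weeks". Baseline is not named.
- Random effects: "The random effects are intercept and slope; which posit that each participant has a “personalized” linear response to treatment".
- Fixed effects: "The fixed effects include site, treatment group, and time since entry, and time interactions, which measure systematic differences in the rate of change". No baseline outcome score is listed.
- Starting level: "The assumption of a common initial mean for all participants is justified by the randomization of participants into treatment groups".

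The baseline outcome is available for everyone randomised. The randomisation section places its collection before allocation ("Once written informed consent has been obtained to participate in the trial, and baseline data collected"), and the participant timeline agrees.

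The power section gives power above .80 for a between-arm difference in change, with f = .10, 350 per arm, 5% attrition, two-sided alpha .05, and correlations of .6 at 4 weeks and .5 at 12 weeks.

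**The concern.** In a model with time since entry, a treatment-group main effect beside group-by-time terms is the arm difference at time 0. If baseline is a response, listing that term lets the arms differ at baseline, which is what the common-mean sentence rules out. If the responses start at week 4, as the first sentence says, the model contains no observed pre-treatment mean. The sentence could then describe only an extrapolated intercept, and the baseline score plays no part.

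Three models therefore fit some of the text, and none fits all of it. They differ in how much of the baseline information they use, and so in the precision of the primary comparison. If the choice is left until data are in hand, it is also a free analytic choice on the primary outcome.

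**Working it through.** **Inputs from the power section:** 350 per arm; 5% attrition, so 350 × 0.95 = 332.5 per arm; two-sided alpha .05; f = .10; r = .6 at 4 weeks.

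**Assumptions:** f = .10 is read as d = 2f = 0.20 in outcome-SD units. The check uses a single week-4 contrast with equal variances, not the full random-slope model.

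**Formulas.** With variance factor v relative to comparing week-4 scores alone:

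- Power = Φ(0.20 × √(332.5/2) / √v − 1.96) = Φ(2.579/√v − 1.96)
- Analysed per arm for 80% power = 2 × (1.96 + 0.8416)² × v / 0.20² = 392.4 × v, rounded up

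**The plan's own figure first.** For a change contrast v = 2(1 − r) = 0.80. Power = Φ(2.883 − 1.96) = 0.822, so the claim of more than .80 reproduces. This does not prove that a change contrast was intended: a between-groups F test on two measurements with r = .6 gives 0.821.

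**The three readings at r = .6:**

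| Reading | v | Power | Analysed per arm for 80% |
|---|---|---|---|
| Responses from week 4 only, baseline unused | 1 | 0.732 | 393 |
| Baseline a response, free group term, arm-by-time contrast | 2(1 − .6) = 0.80 | 0.822 | 314 |
| Common baseline mean imposed, or baseline as covariate | 1 − .6² = 0.64 | 0.897 | 252 |

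Generalised least squares on weeks 0 and 4 returns the same factors for all but the first row: 0.80 for the interaction with a free group term and 0.64 with the common mean imposed. Adding week 8, with an assumed 8-week correlation of .55, leaves these two unchanged. Weeks 4 and 8 alone give 1.00 for the week-4 effect, as in the first row. In a linear-time model on weeks 0, 4 and 8 under the same assumption, imposing the common mean multiplies the variance of the slope difference by 0.762, a cut of about 24%.

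**Sensitivity to r.** The variance ratio of the third reading to the second is (1 − r²) / (2(1 − r)) = (1 + r)/2:

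- r = .5: ratio 0.75, a saving of 25% (power 0.732 against 0.846)
- r = .6: ratio 0.80, a saving of 20%
- r = .7: ratio 0.85, a saving of 15%
- r = .8: ratio 0.90, a saving of 10%

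The protocol gives r = .5 for 12 weeks, so the first line is a bound for the week-4 contrast rather than its planned value. The protocol calls its correlation conservative, so the true saving may be nearer the lower lines.

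**The case against.** A reader might infer that the plan definitely discards baseline precision. The documents do not support that. If the common-mean sentence is what will be fitted, with baseline as a response and no group difference at time 0, the variance factor is already 1 − r² and nothing is lost. This objection stands, and it makes the loss conditional.

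A reader might take the week 4, 8 and 12 sentence to mean that baseline is certainly unused. That is the weakest reading: the same section speaks of an initial mean, time since entry and rate of change, and the power section concerns change. The 0.73 figure belongs to that reading alone at r = .6.

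A reader might also conclude that the sample size is wrong or the estimate biased. Neither follows. The stated power reproduces for a change contrast, and randomisation protects all three analyses from systematic baseline bias. A change contrast does subtract the chance baseline difference; what remains is regression to the mean.

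The size depends on how f is read. Taken as the effect size of a repeated-measures within-between F test, power exceeds 0.999 and the gain is moot.

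It is tempting to turn 314 and 252 into attrition allowances of about 10% and 28% of 350. That treats dropout as lost numbers only. The protocol expects losses from illness or death and does not require questionnaires from those who withdraw from the service, so baseline adjustment does not make such losses harmless.

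Finally, the fixed-effects list is open-ended and a full covariate list may sit in an analysis plan. The absence of a baseline covariate is therefore not a finding by itself. The conflict between sentences that are stated remains.

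**Conclusion.** The section is internally inconsistent about the primary model, and this should be settled before analysis. Under the stated assumptions (d = 0.20, r = .6, 332.5 per arm, one week-4 contrast), power is about 0.82, 0.73 or 0.90 according to which statement governs. Against the change contrast, using baseline fully cuts variance by 20% at r = .6, shrinking to 10% at r = .8. The point concerns precision and an undetermined model. It shows no error in the stated power and no bias.

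**What to change.** Reconcile the model description in one of two ways, keeping site as a fixed effect in both:

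1. Enter baseline as a response with one mean shared by both arms: no group term at time 0, and arm-by-visit terms from week 4.
2. Model the post-baseline scores with the baseline score as a covariate, and delete the common-mean sentence.

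For the week-4 contrast the two have the same efficiency with complete data; with missing scores they can differ, so the text should name one. The cost is wording only: baseline is already collected before randomisation. Neither option addresses bias from informative attrition, which needs its own handling.
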